# Phone calls on Day 3 will be arranged after vaccine administration to ensure completion of the Participant's DC and to check their health status. No deviation will be considered if the phone call could not be completed on the exact date.

@ Only from Adult subjects of 18 to 45 years

\* After visit 4, only concomitant medication related to SAE will be captured

\$ Blood pressure collection is for adult population of 18 years to 45 years

% Urine pregnancy test (UPT) will be performed to all female participants of childbearing age from menarche.

© During city lock down only safety follow up has been done through phone call in V3 and V4. Even the post vaccination blood sample at V4 could not be collected.

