### **Visit 5 - Follow-up visit (Week 24, Day 168 ± 7 days)**

This is the final visit of the study.

- 1) Collect diary card 3 and check with participant/parent(s)/LAR before recording observations in the eCRF
- 2) Perform clinical examination including vital signs, general physical examination
- 3) Collect interval medical history in order to capture any SAEs through interview. Record any SAE and concomitant medications in eCRF
- 4) Ensure source documents are duly completed before the participant/parent(s)/LAR leave the study center
- 5) Participant will be continued to be monitored after study ends for unresolved AE

While in the study the female participant of child bearing age should not get pregnant. As such they should discuss with their study doctor if their current contraception can give them a reliable protection against getting pregnant. If any participant becomes pregnant during the conduct of the study, then the participant would be followed up until delivery and informations will be captured in pregnancy form. Detailed information regarding pregnancy such as method of delivery, duration of pregnancy and outcome to both mother and baby will be captured and mentioned in safety management plan.

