## 7.9 PROTOCOL DEVIATIONS

A protocol deviation is any non-compliance with the clinical trial protocol or GCP by the participant, the investigator, or the study site staff. It is the responsibility of the site investigator to use continuous vigilance to identify and report all major protocol deviations to site IRB and sponsor. Minor protocol deviations could be reported to IRBs along with periodic study report submission as per local IRBs requirements. The site investigator is responsible for knowing and

adhering to the site IRB requirements. The IVI Study Medical Monitor will report all protocol deviations to IVI IRB.

Major deviations are defined as those jeopardize the safety or rights of the participant or the scientific integrity of the study which may be applicable to cases listed below.

- Violation of inclusion and exclusion criteria
- Vaccination with wrong vaccine as defined in the protocol
- Visit outside window for the immunogenicity assessment after discussion with the study medical monitor
- Missed samples for immunogenicity

Major protocol deviations thought to affect the scientific integrity of the study will be reported and discussed with investigator, monitor, sponsor, and statistician for their exclusion from the per protocol analysis. For minor protocol deviations considered not to affect the scientific integrity of the study, the extent of deviation or delay as well as reason will be accurately documented.

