#### 11.4 ANALYSIS DATASETS

The Full Analysis set (FAS) is a modified intention-to-treat (m-ITT) analysis set that will include all participants randomized in the study who received at least one dose of investigational vaccines. This data set will be used for demographic information and safety analysis.

The immunogenicity analysis set is a subset of FAS of those who is randomized, received at least one dose of investigational vaccines and have at least one post-baseline immunogenicity data available.

The per-protocol (PP) analysis set will be a subset of the immunogenicity analysis set who do not have protocol violations (defined as major deviation from the protocol compromising the scientific integrity of the study) with regards to the inclusion/exclusion criteria, are compliant with study procedures, completed all visits as scheduled and received the correct vaccinations.

The immunogenicity analysis set will be used for the primary analysis of the immunogenicity endpoints. A sensitivity analysis using the PP analysis sets will be conducted for the primary and secondary immunogenicity endpoints.

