#### 11.5.7 PLANNED INTERIM ANALYSIS

A primary analysis will be performed after all participants complete week 4 visit post test/control vaccine dose. After that the final analysis will be performed when all participants complete week 24 visit. There will be two CSRs planned i.e. pCSR for the primary analysis and fCSR for final analysis.

---

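### The per-protocol set requires all scheduled visits, including Week 24, although it serves only Day 28 endpoints and is first needed at the Week 4 analysis

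*Protocol*

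**What the plan says.** Section 11.4 builds the per-protocol set as a subset of the immunogenicity analysis set. Members must have no protocol violations on eligibility and must be participants who "are compliant with study procedures, completed all visits as scheduled and received the correct vaccinations". The visit condition stands by itself and has no end point.

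The same section gives the set its use: "A sensitivity analysis using the PP analysis sets will be conducted for the primary and secondary immunogenicity endpoints". The main comparison uses a different set: "The immunogenicity analysis set will be used for the primary analysis of the immunogenicity endpoints". Section 11.5.6 also counts the per-protocol set in the disposition summary, but no other analysis uses it.

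On timing, section 11.5.7 states: "A primary analysis will be performed after all participants complete week 4 visit post test/control vaccine dose". It adds: "There will be two CSRs planned i.e. pCSR for the primary analysis and fCSR for final analysis". Section 11.2 says the same about timing, and says that immunogenicity data are included again in the final analysis.

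Table 2 schedules Visit 5 at Day 168 ± 7, and section 7.6.3 says of it: "This is the final visit of the study". Blood is drawn at Day 0 and at Visit 4 (Day 28 ± 3) only, from adults only.

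Section 7.9 lists the cases that may count as major deviations: eligibility violations, "Vaccination with wrong vaccine as defined in the protocol", a visit outside the window for the immunogenicity assessment, and missed immunogenicity samples. Exclusions from the per-protocol analysis are then settled by discussion. Visit 5 is not listed.

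**The concern.** A per-protocol set for a Day 28 titre should depend on what could affect that titre: eligibility, the vaccine given, the two samples and their timing. Attendance 20 weeks later cannot change a sample already drawn. Making it a condition has three consequences.

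- The set cannot be settled at the Week 4 analysis, which section 11.2 says is done to start the licensure process.
- At the final analysis, participants with valid data are removed because of events after the outcome was measured.
- The same endpoint can have two different per-protocol estimates, one in each report, for a reason unrelated to immunogenicity.

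At stake is the usefulness of the planned sensitivity analysis at the time the equivalence result is reported. The primary comparison itself is not at stake.

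**Working it through.** The protocol gives no figure for the per-protocol set, so there is none to reproduce. The check has two parts.

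**1. How many participants have reached Visit 5 at the Week 4 cut?**

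Inputs: planned first enrolment January 2020 and last enrolment May 2020 (Synopsis, Study Period); Visit 4 at Day 28 ± 3 and Visit 5 at Day 168 ± 7 (Table 2). Assumptions: enrolment is uniform over E days, and the cut falls when the last participant completes Visit 4. Exact calendar days are not stated, so E is given as a range.

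With nominal visit days the cut is at day E + 28, and anyone enrolled at least 168 days earlier has had Visit 5:

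share = max(0, (E + 28 − 168)/E) = max(0, 1 − 140/E)

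With the windows at their most favourable (last Visit 4 at day 31, Visit 5 at day 161):

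share = max(0, (E + 31 − 161)/E) = max(0, 1 − 130/E)

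| Enrolment period | Nominal days | Most favourable windows |
|---|---|---|
| 91 days (31 Jan to 1 May) | 0% | 0% |
| 121 days (15 Jan to 15 May) | 0% | 0% |
| 151 days (1 Jan to 31 May) | 1 − 140/151 = 7% | 1 − 130/151 = 14% |

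The lockdown may have lengthened enrolment. The protocol does not say by how much, so these are assumed durations with nominal days:

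- 26 weeks (182 days): 1 − 140/182 = 23%
- 39 weeks (273 days): 1 − 140/273 = 49%
- 52 weeks (364 days): 1 − 140/364 = 62%

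Under the planned dates the literal set is empty or a small early-enrolled group. Under longer enrolment it is still partial and still selected by enrolment date.

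**2. Do the sections agree?**

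| Question | 11.4 | 7.9 |
|---|---|---|
| Which visits count? | All scheduled visits, with no cut-off | For timing, only the immunogenicity visit window |
| Does a missed or late Visit 5 exclude? | Yes, read literally | Not listed |
| How is exclusion decided? | By a stated condition | By discussion of major deviations |

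Take an adult with the correct vaccine, a Day 0 sample, an in-window Day 28 sample and a Visit 5 outside Days 161 to 175. Under 11.4 this person leaves the per-protocol set. Under the listed items in 7.9 nothing excludes them. Neither section says that the set stops at Week 4.

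The phone visits raise a smaller question of the same kind. A footnote to Table 2 records: "During city lock down only safety follow up has been done through phone call in V3 and V4". Another footnote says that an inexact date for the Day 3 call is not a deviation. There is no such statement for a Visit 3 held by phone, so its status under the visit condition is left open.

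**The case against.** The best defence is that the clause should be read in context. Section 11.2 limits the primary analysis to data up to Week 4, so visits not yet due might naturally be ignored. Section 11.4 ties violations to major deviations that compromise scientific integrity, and 7.9 lists only visit and sample items that concern immunogenicity. Section 11.2 also leaves further detail to a statistical analysis plan that is not at hand.

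Part of this stands. The intention was probably narrower than the wording, and a reader might infer too much in saying that the set could not be formed under any reading. But if the rule means visits due so far, Visit 5 falls due by the final analysis, where immunogenicity data are included again. Membership would then still change between the two reports. Nor is this detail left for later: 11.4 states a rule, and it differs from 7.9.

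Four stronger inferences are tempting and are not supported.

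- **Loss of power.** Section 11.1 has one 10% dropout allowance, not split by visit, and no Week 24 attrition figure. The loss from the set cannot be calculated, and no power requirement is attached to it.
- **A large loss through phone visits.** Adults whose Visit 4 was held by phone had no blood drawn then, and the protocol says it will not be drawn later, so they are already outside the immunogenicity analysis set. Only those with a phone Visit 3 and an on-site Visit 4 draw are in question. Their number is not given and may be small.
- **Errors in the main set all favour equivalence.** A swap between the two Vi-DT formulations would pull the arms together, but control vaccine given by mistake in one Vi-DT arm could push them apart. Eligibility violations have no fixed direction, and no error rates are given.
- **Equivalence must be shown in both sets.** The protocol names one primary set in advance and plans the per-protocol analysis as a sensitivity analysis. That choice is coherent. Asking for agreement of both sets is a debatable design preference.

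**Conclusion.** The point holds as a defect in a stated rule. Read literally, the visit condition in 11.4 extends to Day 168 for a set whose only analytic use is Day 28 endpoints. It prevents membership from being settled at the Week 4 analysis, lets a later event remove a valid titre, allows two per-protocol ratios for one endpoint, and disagrees with 7.9.

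The timing result of 0% to about 14% rests on uniform enrolment within the planned January to May 2020 dates. Longer enrolment raises the share (23% to 62% at 26 to 52 weeks, assumed) but does not complete the set. The conclusion on wording and internal conflict needs none of these assumptions.

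The reach is limited to a sensitivity analysis. The main GMT comparison in the immunogenicity analysis set is not affected.

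**What to change.** In 11.4, replace the visit condition by one limited to what bears on the two samples: eligible, correct vaccine received, Day 0 sample taken before vaccination, Visit 4 sample within its window, and no other major deviation up to Visit 4. State that Visit 5 attendance and a Visit 3 held by phone do not count. Align 11.4 and 7.9 so that both give the same set. Fix membership blind to allocation before the Week 4 analysis, and use that same membership in both reports.

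The cost is a wording change in the protocol, carried into the analysis plan. It needs no new data and leaves the primary analysis as it is. Compared with the literal rule, it can only return to the set participants who would have been lost through the later visit or the phone contact.

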## 11.5 DESCRIPTION OF STATISTICAL METHODS

### 11.5.1 GENERAL APPROACH

This study is a randomized, observer-blinded phase III study in healthy participants with age 6 months to 45 years old at the time of vaccination of investigational vaccine to assess the safety and the equivalence of immunogenicity of multi-dose formulation compared to single-dose formulation of Vi-DT in an adult participants (18 -45 year age stratum).

Unless specified as in section 11.3, for equivalence test, the significance level is 5% with two sided test.

Analysis of covariance will be used to adjust for baseline titers, stratification and imbalances in baseline characteristics if necessary.

Missing immunogenicity data will not be imputed for the analysis. If missing data is more than 10%, the analysis of missing pattern will be assessed and a multiple imputation technique will be utilized as a sensitivity analysis.

### 11.5.2 BASELINE DESCRIPTIVE STATISTICS

Demographic characteristics and other baseline data of participants enrolled will be tabulated by vaccine group and overall. Continuous variables such as age, height and weight will be summarized by number of participants, mean, standard deviation, median, minimum and maximum. Categorical variables such as sex will be summarized by frequency and percentage in each vaccine. If a difference in baseline characteristics among groups is suspected, the statistical significance will be compared using ANOVA for continuous variables, and Chi-square test or Fisher's exact test for categorical variables.

### 11.5.3 SAFETY ANALYSIS

The following safety endpoints will be descriptively summarized by each formulation and overall and within each age stratum.

- Local and systemic solicited adverse events during the 7 days after each dose:

- the solicited local reactions at the site of injection: pain, tenderness, erythema/redness, swelling/ induration, pruritus and
- solicited Systemic reactions (adapted to each age group): fever, lethargy, irritability, nausea/vomiting, arthralgia, diarrhea, drowsiness, loss of appetite, chills, headache, fatigue, myalgia and persistent crying
- Unsolicited adverse events during 4 weeks (28 days) after vaccination
- Serious Adverse Events during the entire study period

Number of AEs and proportion of participants with safety endpoints after Vi-DT (MD), Vi-DT (SD), and Control vaccine will be summarized and the 95% confidence interval of the proportion will be calculated for Vi-DT (MD), Vi-DT (SD), and Control vaccine within each age stratum as well as overall strata.

Occurrence of any SAE during the study and AE that lead participant early drop out of the study will be listed.

---

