## Group Allocation

| Group of Vaccinees and age group                      | Age Strata  | N*  | D0                                |
|-------------------------------------------------------|-------------|-----|-----------------------------------|
| Group A
750 participants
(6 mo - 45 yrs) | 18-45 yrs   | 250 | (25 µg 0.5 mL)                    |
|                                                       | 2- <18 yrs  | 250 | (Vi-DT)                           |
|                                                       | 6 mo-<2 yrs | 250 | Multi dose formulation            |
| Group B
750 participants
(6 mo - 45 yrs) | 18-45 yrs   | 250 | (25 µg 0.5 mL)                    |
|                                                       | 2- <18 yrs  | 250 | (Vi-DT)                           |
|                                                       | 6 mo-<2 yrs | 250 | Single dose formulation           |
| Group C
300 participants
(6 mo - 45 yrs) | 18-45 yrs   | 100 | Control                           |
|                                                       | 2- <18 yrs  | 100 | (Meningococcal Conjugate vaccine) |
|                                                       | 6 mo-<2 yrs | 100 |                                   |

\* Age Strata wise number of enrolled subjects may be adjusted during the actual enrollment.

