### Secondary

- Demonstrate the immune equivalence as measured by seroconversion rates of anti-Vi IgG ELISA antibody titres of multi dose formulation against single dose formulation of Vi-DT vaccine (18-45 year age stratum) 4 weeks after single dose
- Describe safety profile in all age strata combined (age 6 months - 45 yrs old) and in each age stratum#, 4 weeks after single dose of MD/SD formulation/control (Meningococcal conjugate Vaccine )

# Age strata of 6 months to less than 2 years, 2 years to less than 18 years, and 18 years to 45 years.

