#### Secondary Endpoints

- Seroconversion rates (defined as a 4-fold increase of serum anti-Vi IgG antibody titer from baseline) of anti-Vi IgG ELISA antibody titers at 4 weeks (28 days) after vaccination with Vi-DT(MD) / Vi-DT (SD) compared to baseline (D0) [18-45 year age stratum]
- Comparison of safety of V-DT compared to control: Vi-DT MD and SD will be compared separately to control vaccine and will be compared by age strata at 4 weeks after vaccination
  - Local and systemic solicited adverse events during the 7 days after vaccination  
(Refer to Table 5 and 6 for details of grading of AEs)

- Solicited local reactions at the site of injection: pain, tenderness, erythema/redness, swelling/ induration, pruritus
- Solicited Systemic reactions (adapted to each age group): fever, lethargy, irritability, nausea/vomiting, arthralgia, diarrhea, drowsiness, loss of appetite, chills, headache, fatigue, myalgia and persistent crying
- Unsolicited adverse events during 4 weeks (28 days) after vaccination
- Serious Adverse Events during the entire study period

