## 5.3 MEASURES TO MINIMIZE BIAS

### 5.3.1 RANDOMIZATION/MASKING PROCEDURES

The randomization list will be generated by an IVI independent statistician who is not directly involved in the study conduct. Eligible participants will be assigned to receive single dose of Vi-DT test vaccine (either from multidose or single dose formulation) or control vaccine in a (2.5) : (2.5) : 1 ratio (i.e. 750, 750, and 300 participants respectively). The randomization list will contain sequential numbers unique to each participant and the block randomization process will be employed to ensure an effective balance between the interventions.

Only the independent statistician will have a complete set of randomization lists. The individual site lists will be kept under lock and key by the pharmacy staff at all clinical sites. At the end of the study after unblinding of the participants, the lists will be returned to the statistician.

Two types of randomization list, one with randomization number only, and the second with randomization number and vaccine allocation will be prepared. Participants in the study will be randomized into three treatment groups within each age stratum: 6 to less than 24 months, 2 to less than 18 years, and 18 to 45 years. Randomization list “without the vaccine allocation” with numbers will only be shared with the blinded trial staff, for enrolling the trial participants and assigning them the randomization number. The randomization list “with the vaccine allocation” will be shared with the unblinded vaccine administrator (study nurse/pharmacist). If feasible, a web based randomization system may be provided to each site and in that case paper based randomization list will not be used.

Upon enrollment, in order to receive the study vaccine, participants will be sent to the vaccine administrator with their randomization number. The unblinded study nurse/pharmacist located in

a different room will administer vaccine(s) to the participant according to the randomization list. The randomization number of the participant receiving the study vaccine will be written on the empty vaccine vial and on the vaccine accountability log for record and reconciliation.

Trial staff other than the unblinded study staff will remain blinded to vaccine administration. The unblinded study nurse/pharmacist will not be involved in the evaluation of vaccine safety and will not discuss with the investigator and clinical staff about vaccines administered.

---

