## 11.2 STATISTICAL ANALYSIS PLAN

The statistical analysis will focus on comparisons of immunogenicity of Vi-DT (MD; Group A) and Vi-DT (SD; Group B) at 4 weeks post vaccination. Safety of Vi-DT will be assessed by descriptively comparing incidence of common solicited, unsolicited and serious AE between Vi-DT and Control and any incidence of unexpected AE. A primary analysis will be performed after all participants complete week 4 visit post test/control vaccine dose in order to initiate the test vaccine licensure process. Immunogenicity and safety data up to week 4 will be included in this analysis and this will be done in a way so that the study and study personnel remain blinded to the allocation of test/control vaccine until the end of the study. The final analysis will be performed when all participants complete week 24 visit. Immunogenicity and safety data up to week 24 will be included in the final analysis.

Additional statistical analysis details will be described in the statistical analysis plan (SAP) (which will be finalized prior to database lock) and any deviation(s) from the original SAP will be described and justified in the final study report.

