#### ***Safety endpoints are as follows:***

As a part of immediate reaction one participant who received 1st dose of Vi-DT reported erythema/redness, fever within 30 min.

Solicited AEs: In post first dose, a higher percentage in Vi-DT combined group who experienced AEs compared to placebo group (25.88% vs. 19.30%) was observed. In post second dose, a lower percentage in Vi-DT two-dose group who experienced AEs compared to placebo (6.48% vs. 9.09%) was observed.

Unsolicited AEs: Within 4 weeks post first dose, a lower percentage in Vi-DT combined group experienced AEs compared to Placebo (61.40% vs. 68.42%). Within 4 weeks post second dose, a higher percentage in Vi-DT two-dose group experienced AEs compared to placebo (30.56% vs. 27.27%).

Medically significant unsolicited AEs rates which happened beyond 4 weeks post each dose are lower in percentage in Vi-DT combined group compared to placebo group during the entire study period (22.81% vs. 38.60%).

In terms of SAE, comparable percentages of SAEs between Vi-DT combined group and placebo group within 4 weeks after either dose (0.88% vs. 1.75%) and during entire study period (4.39% vs. 5.26%) were reported.

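### The safety endpoint is a comparison of each Vi-DT formulation with control, but section 11.5.3 puts confidence intervals only on each arm's own proportion; a descriptive risk difference should be added

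*Protocol*

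**What the plan says.** In the synopsis and in section 5.1, the secondary endpoints include a comparison of safety against control: "Vi-DT MD and SD will be compared separately to control vaccine and will be compared by age strata at 4 weeks after vaccination". Section 11.2 also describes a between-arm exercise, namely "descriptively comparing incidence of common solicited, unsolicited and serious AE between Vi-DT and Control".

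The objectives in the synopsis and section 4 are softer: "Describe safety profile in all age strata combined" and in each age stratum. The synopsis and section 5.2 speak of a descriptive evaluation and say that the control group is there to show background safety events.

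Section 11.5.3 names the statistics: numbers of events, the proportion of participants with each safety endpoint, and an interval for each proportion. In its words, "the 95% confidence interval of the proportion will be calculated for Vi-DT (MD), Vi-DT (SD), and Control vaccine within each age stratum", and also across strata. It names no difference, ratio or interval for MD against control or SD against control. No safety hypothesis or margin appears anywhere. Section 11.2 leaves further detail to a SAP that is not at hand.

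**The concern.** The endpoint is a contrast between two arms, whereas the named output is three one-sample estimates. A descriptive comparison also needs an estimate of the thing compared, with its uncertainty. The protocol gives one where it wants one: section 11.5.5 specifies a confidence interval for the difference in seroconversion. For safety, 11.5.3 is not silent on intervals; it places them on the individual proportions.

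With only per-arm intervals printed, some readers will compare them by eye. Two separate 95% intervals can overlap although the 95% interval for the difference excludes zero. In a safety table, that habit errs towards overlooking an excess over background. At stake is how clearly the report shows the comparison promised in section 5.1. The primary GMT conclusion is not involved.

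**Working it through.** **The plan's own safety figure.** Section 11.1 sizes the control group by the rule of three: 3/300 = 1.00%. The exact one-sided 95% bound is 1 − 0.05^(1/300) = 0.99%, and the chance of at least one event at a true rate of 1% is 1 − 0.99^300 = 95.1%. The figure reproduces. It concerns a single arm and says nothing about the precision of a contrast.

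**Inputs**
- Arm sizes: 750 per Vi-DT formulation and 300 control overall (section 5.3.1); 250 and 100 per age stratum (Table 1). Stratum sizes may shift under the age-strata reassignment, so the per-stratum results are for the planned sizes.
- Illustrative rates: 25.88% for Vi-DT and 19.30% for placebo, solicited events after the first dose (Appendix ii: "a higher percentage in Vi-DT combined group who experienced AEs compared to placebo group (25.88% vs. 19.30%) was observed"). Using them for this trial is an assumption.

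**One data set at 750 versus 300.** 0.2588 × 750 ≈ 194 and 0.1930 × 300 ≈ 58.
- Exact (Clopper-Pearson) intervals: 194/750 = 25.9% (22.8% to 29.2%); 58/300 = 19.3% (15.0% to 24.3%). They overlap between 22.8% and 24.3%. Wald and Wilson intervals overlap too.
- Difference: 25.87 − 19.33 = 6.53 points.
- The Newcombe interval uses the Wilson limits, 22.86% to 29.12% and 15.26% to 24.18%:
  - lower: 6.53 − √[(25.87 − 22.86)² + (24.18 − 19.33)²] = 6.53 − 5.70 = 0.8
  - upper: 6.53 + √[(29.12 − 25.87)² + (19.33 − 15.26)²] = 6.53 + 5.21 = 11.7

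The difference interval excludes zero while the per-arm intervals overlap.

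**One data set at 250 versus 100.** 65/250 against 19/100 gives 7.0 points, Newcombe −3.1 to 15.7. This is inconclusive either way.

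**How often the two displays disagree**, by exact enumeration of both binomials at the assumed rates:

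| Sizes | Per-arm intervals separate | Newcombe interval above 0 | Overlap and Newcombe above 0 |
|---|---|---|---|
| 750 vs 300 | 31% | 62% | 31% |
| 250 vs 100 | 6% | 24% | 18% |

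In these settings, separation never occurs without a Newcombe interval above zero, so the last column is the difference of the two before it (62.3 − 31.1 = 31.2; 24.5 − 6.4 = 18.1). With no true difference (25.88% in both arms, 750 versus 300), upward separation occurs in 0.3% of trials and a Newcombe interval above zero in 2.4%.

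**Less dependence on one pair of rates.** The smallest observed excess needed, for control rates of 5% to 30%:
- 750 versus 300: about 3.7 to 6.4 points for the difference interval to exclude zero, and about 5.3 to 9.1 points for the per-arm intervals to separate.
- 250 versus 100: about 7.4 to 11.6 points and about 10.6 to 16.4 points.

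**The case against.** The case against is substantial, and much of it stands.

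- **Safety is descriptive.** The objective says so, there is no safety hypothesis, and section 11.2 describes the comparison as descriptive. Proportions side by side with intervals are a legitimate descriptive display, and a reader with the counts and denominators can work out the difference. This stands, and it limits the point to an improvement.
- **It could be left to the SAP.** In part. Nothing in 11.5.3 forbids a contrast, and a SAP could add one. But 11.5.3 does specify which intervals to compute, and a SAP that followed it to the letter would not estimate what section 5.1 names.
- **No overlap rule exists.** A reader might infer that the trial will judge safety by whether intervals overlap. The protocol says no such thing; the figures above show only what an informal reading by eye would do.
- **A real excess would usually be hidden.** A reader might infer this too, but the figures do not support it. Overlap together with a difference interval above zero occurs in 31% of trials overall and 18% per stratum, a minority in both cases. Within strata, the difference interval itself misses the assumed excess in about 76% of trials.
- **The rates are borrowed.** They compare Vi-DT with placebo at 6 to 23 months of age. Here the control is an active vaccine and ages run to 45 years. The Phase I trial against an active comparator (section 3.2) shows no consistent excess: 54.17% vs 50%, 37.5% vs 45.8%, and 25% vs 25%, or 28/72 vs 29/72 in all. Unsolicited events after the first Phase II dose ran the other way (61.40% vs 68.42%). The rates illustrate; they do not predict.
- **The shifting age mix.** One might infer that moving enrolment between strata biases a crude pooled contrast with control. It does not by itself, because allocation is 2.5 : 2.5 : 1 within each stratum.

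**Conclusion.** The mismatch is real and modest. Section 5.1 and the synopsis promise a separate comparison of each formulation with control by age stratum, section 11.2 asks for a descriptive comparison, and 11.5.3 provides only per-arm proportions with per-arm intervals. The named contrast and its uncertainty are not directly estimated by the stated output.

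Its size depends on assumed rates. At 25.88% versus 19.30% and the planned overall sizes, the two displays would disagree in about three trials in ten, and in fewer than two in ten within a stratum. No data are lost and no stated conclusion is wrong. Data Safety Monitoring Board oversight and the serious-event listings are unaffected.

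**What to change.** In section 11.5.3, add the risk difference MD minus control and SD minus control, each with a 95% confidence interval (Newcombe or Miettinen-Nurminen), for the solicited, unsolicited and serious adverse event summaries. Give it within each age stratum and overall; stratifying the overall estimate by the randomisation age strata is good practice, though not needed to remove bias. Label these intervals descriptive and unadjusted for multiplicity, in line with section 11.5.9, without p-values. Keep the per-arm intervals. The alternative is to reword the endpoint in the synopsis and section 5.1 so that it no longer promises a comparison.

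The cost is some wording and extra table columns, with no new data. The drawback is many more intervals. Of the 18 solicited reactions listed, 14 are collected at all ages; two contrasts in three strata and overall already give 14 × 2 × 4 = 112, and some will exclude zero by chance. Giving the contrasts first for the summary categories (any solicited local, any solicited systemic, any unsolicited, any serious) limits this.
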